## Abstract

**Background:**

Shorter periods of hospitalisation and increasing warfarin use have placed stress on community-based healthcare services to care for patients taking warfarin after hospital discharge, a high-risk period for these patients. A previous randomised controlled trial demonstrated that a post-discharge service of 4 home visits and point-of-care (POC) International Normalised Ratio (INR) testing by a trained pharmacist improved patients' outcomes. The current study aims to modify this previously trialled service model to implement and then evaluate a sustainable program to enable the smooth transition of patients taking warfarin from the hospital to community setting.

**Methods/Design:**

The service will be trialled in 8 sites across 3 Australian states using a prospective, controlled cohort study design. Patients discharged from hospital taking warfarin will receive 2 or 3 home visits by a trained 'home medicines review (HMR)-accredited' pharmacist in their 8 to 10 days after hospital discharge. Visits will involve a HMR, comprehensive warfarin education, and POC INR monitoring in collaboration with patients' general practitioners (GPs) and community pharmacists. Patient outcomes will be compared to those in a control, or 'usual care', group. The primary outcome measure will be the proportion of patients experiencing a major bleeding event in the 90 days after discharge. Secondary outcome measures will include combined major bleeding and thromboembolic events, death, cessation of warfarin therapy, INR control at 8 days post-discharge and unplanned hospital readmissions from any cause. Stakeholder satisfaction will be assessed using structured postal questionnaire mailed to patients, GPs, community pharmacists and accredited pharmacists at the completion of their study involvement.

**Discussion:**

This study design incorporates several aspects of prior interventions that have been demonstrated to improve warfarin management, including POC INR testing, warfarin education and home visits by trained pharmacists. It faces several potential challenges, including the tight timeframe for patient follow-up in the post-discharge period. Its strengths lie in a strong multidisciplinary team and the utilisation of existing healthcare frameworks. It is hoped that this study will provide the evidence to support the national roll-out of the program as a new Australian professional community pharmacy service.

**Trial Registration:**

Australian New Zealand Clinical Trials Registry Number 12608000334303.

## Background

Warfarin has been in widespread use since the 1950s and is currently the most commonly prescribed vitamin K antagonist worldwide [1]. The use of warfarin in Australia is now increasing at approximately 8-10% per year [2,3], largely because of its proven benefits in preventing stroke in patients with atrial fibrillation (AF) and the increasing prevalence of this condition [1,4-7].

### Complications of warfarin therapy

Warfarin is recognised as a high-risk drug [4,8-14]; it is 1 of the top 10 agents most frequently associated with adverse drug events [15]. A number of studies have reported that the risk of warfarin-related bleeding is highest early in the course of therapy [16-22], with the risk for major bleeding during the first month of therapy approximately 10 times the risk after the first year [16-18,23].

Traditionally, anticoagulant therapy in Australia is managed in the community by general practitioners (GPs) and pathology providers. The combination of shorter periods of hospitalisation and increasing usage of warfarin has placed stress on these community-based health services to care for anticoagulated patients after discharge from hospital [24]. There is often poor discharge planning [25], insufficient communication between the hospital and GPs at hospital discharge, and GPs may extend the interval of INR monitoring too early and/or increase warfarin dosages too quickly in newly initiated patients [26].

Hospitalisation has been demonstrated to be an independent cause of reduced anticoagulant control [27]. Patients require more frequent International Normalised Ratio (INR) monitoring in the post-discharge period due to INR fluctuations resulting from their recovery from illness and alterations in medication regimens. Communication difficulties and the potential for misinterpretation of information following discharge have been shown to result in dosage errors [28].

Frequent laboratory testing also represents a significant burden and may be unrealistic for patients who may be dependent on others for transportation and may be challenged by physical limitations to mobility. These impediments to frequent testing are especially relevant for those patients who live in rural areas [29].

### Pharmacist involvement in warfarin management

Literature from Australia [30-32] and overseas [33-35] describes a role for pharmacists in anticoagulation management, particularly in the setting of anticoagulation clinics. In the post-discharge setting, a randomised controlled trial (RCT) of home visits and point-of-care (POC) INR testing by a pharmacist improved the initiation of warfarin therapy and resulted in a significant decrease in haemorrhagic complications in the first 3 months of therapy [36]. One hundred and twenty eight patients initiated on warfarin in hospital and subsequently discharged to GP care in southern Tasmania received 4 visits on alternate days, with the initial visit 2 days after discharge from hospital. At Day 8 post-discharge, 67% of the intervention patients had a therapeutic INR, compared with 42% of control patients (p < 0.005). Also, 26% of the control patients had a high INR, compared with only 4% of intervention patients [36].

### Justification for this trial

While the previously described RCT was highly successful, it involved only 1 dedicated pharmacist researcher and a limited geographical area. In considering national implementation of the service, the intensity of the 4-visit model may not prove sustainable; thus, a trial investigating 2-visit and 3-visit models is considered necessary. It is also hoped that by integrating the warfarin management service into the existing Home Medicines Review (HMR) program, funded by the Australian Government Department of Health and Ageing and described below, sustainability of the service will be assured.

### Objectives

The objective of this trial is to develop and implement a sustainable program to enable the smooth transition of both newly anticoagulated patients and those already taking warfarin from the hospital to community setting. The aim is to assess whether pharmacist follow-up, using 2 intensities of service across a diverse sample of patients, leads to safer and more effective initiation of anticoagulation, and is valued and welcomed by patients and their GPs and community pharmacists.

## Methods/Design

### Overview

In summary, the post-discharge warfarin management service consists of referral of patients discharged from hospital taking warfarin to, and home follow-up by, a pharmacist in the immediate post-discharge period. Suitable and consenting patients will receive either 2 or 3 home visits by an 'accredited pharmacist', an experienced, mobile pharmacy practitioner, within their first 8 to 10 days post-discharge. The visits will involve a HMR to identify and resolve any post-discharge medication-related issues, warfarin education and the provision of resources depending on the patient's understanding of their warfarin therapy, and POC INR monitoring. The study model is displayed in Figure 1.

**Figure 1 F1:**
[figure not shown]
**Study model**.

The service is collaborative in nature, facilitated by the patients' community pharmacy, with the results of the INR monitoring and need for dose adjustment discussed with the patients' GPs. This complies with Australian legislative requirements that preclude pharmacists from independently recommending dose adjustments to patients. After the post-discharge period, full care will be returned to the patients' community healthcare providers. The outcomes of patients receiving the service will be compared with those receiving 'usual care'; that is INR testing and warfarin management by GPs and pathology providers, in a prospective, controlled cohort study.

### The HMR program and accredited pharmacists

As stated above, the study utilises the existing Australian HMR program, a program "designed to assist consumers living at home to maximise the benefits of their medication regimen and prevent medication-related problems" [37]. A HMR involves the patient, after referral by their GP, being visited at home by an 'accredited' pharmacist who reviews their medication regimen, delivers education and provides the GP with a report and management suggestions. The GP and patient then agree on a medication management plan. The process is facilitated by the patient's regular community pharmacist, which further assists in the development of cooperative working relationships between the members of the patient's healthcare team.

An 'accredited' pharmacist is "an experienced pharmacist who has undertaken specified education programs or examinations, approved by the Australian Association of Consultant Pharmacy (AACP) or the Society of Hospital Pharmacists of Australia (SHPA)", as well as completing continuing specified professional education and regular reaccreditation [37].

### Setting

The program will be implemented and trialled at 8 hospital sites in the Australian states of New South Wales, South Australia and Tasmania across a mix of Pharmacy Access/Remoteness Index of Australia (PhARIA) classes. The PhARIA classification provides a standardised measurement of the physical and professional remoteness of pharmacies throughout Australia [38]. It is a composite index, incorporating measurements of general remoteness with a component of professional isolation represented by the road distance to the 5 closest pharmacies [38]. The characteristics of the 8 hospitals are detailed in Table 1.

**Table 1 T1:** Characteristics of the study sites

Study Site	Location	Number of beds (approx.)	PhARIA Class
Royal Hobart Hospital	Hobart, Tasmania	450	1

North West Regional Hospital	Burnie, Tasmania	160	2

Royal North Shore Hospital	St Leonards, New South Wales	600	1

Wollongong Hospital	Wollongong, New South Wales	511	1

Concord Repatriation Hospital	Concord, New South Wales	238	1

Royal Adelaide Hospital	Adelaide, South Australia	650	1

Flinders Medical Centre	Bedford Park, South Australia	516	1

Whyalla Hospital and Health Service	Whyalla, South Australia	88	4

### Pre-implementation planning

Prior to trial implementation, project officers will be recruited for each of the 8 study sites. Liaison will be undertaken with key stakeholders at these sites to ensure complete dissemination of study information. Meetings and information evenings for GPs and pharmacists will be organised and conducted at each site, and details for email-outs, inclusions for newsletters and on websites will be prepared.

### Accredited pharmacist training

Accredited pharmacists interested in participating in the study will be identified and required to complete the "Anticoagulation Education Program for Accredited Pharmacists". This program, developed in collaboration with consultant haematologists and general physicians, is designed to provide the pharmacists with the additional training required to engage confidently in any discussions with GPs and other healthcare professionals regarding warfarin dosing that may arise during their involvement in the study. This program consists of 3 DVD-based modules of narrated Microsoft PowerPoint^® ^presentations, with accompanying supporting material on CD (slides of the presentations and copies of several important references) and a comprehensive resource manual. Participants will be allowed approximately 8 weeks to complete the 3 modules before attending a single, 2-hour hands-on training session in their local area. This session will offer the opportunity to practice INR monitoring with a CoaguChek^® ^XS monitor (Roche Diagnostics), and receive training in the study methodology. Successful completion of the program will be formally recognised by AACP as a contribution towards each pharmacist's mandatory annual continuing professional development requirements.

Assessment of participating pharmacists' understanding and ability to apply the program content will be undertaken via a paper-based short answer assignment on Modules 1 and 2, and an additional assignment of 5 warfarin dosing scenarios. Participants will be required to offer a dose suggestion based on the scenario and their justification for their response; their responses will be compared with the expert authors' recommendations.

### Quality control (QC) plan

The CoaguChek XS^® ^POC INR monitoring system will be utilised during this study. The researchers have extensive experience in the use of these monitors in research and practice settings, and their accuracy and ease of use have previously been proven in laboratory-based performance verification studies [39], in the hands of trained healthcare professionals in GP surgeries, community pharmacies and hospital outreach settings [30,40], when used by trained patients undertaking patient self-monitoring [41] and in special groups, such as cancer patients [42].

While the internal quality control (IQC) systems in the CoaguChek XS^® ^test strips ensure the precision of testing [43], external QC (EQC) procedures are required to ensure the accuracy of the results obtained. A QC plan for the study has been devised in collaboration with consultant haematologists and the Chief Hospital Scientist from the Royal College of Pathologists of Australasia (RCPA) Haematology Quality Assurance Program. The QC plan is composed of 2 major components: accredited pharmacist training (demonstrated competence in the use of the CoaguChek^® ^XS INR monitor) and EQC. Additionally, there are 2 facets to EQC:

1. Enrolment of the study monitors in the RCPA Quality Assurance Program, where each monitor will be subjected to testing at pre-specified times during the course of the intervention; and

2. Comparison with laboratory INR results. Each accredited pharmacist, a minimum of once during the intervention phase, will be required to validate their technique against a laboratory INR result by arranging with a patient to perform a POC INR as close as possible to, but definitely within 4 hours of, a pathology INR test. A deviation of the POC INR result of more than 15% from the laboratory result will result in the accredited pharmacist being required to demonstrate their INR monitoring technique to the project officer's satisfaction, and re-testing of the monitor in question using another monitor as the comparator, and its subsequent removal from the study if a further significant deviation is demonstrated. INR differences of up to 15% are considered acceptable for clinical purposes, and may also be demonstrated between tests on the same sample in different pathology laboratories due to differences in the collection and testing process [44].

### Ethics approval

Ethics approval has been obtained from the Tasmanian Health and Medical Human Research Ethics Committee (Approval Number: H0010105); the Flinders Medical Centre Clinical Research Ethics Committee (Clinical Drug Trials Committee) (231/08); the Royal Adelaide Hospital Research Ethics Committee (080910); the University of South Australia Human Research Ethics Committee (P252/08); and the Sydney South West Area Health Service Human Research Ethics Committee at Concord Repatriation General Hospital (HREC 08/CRGH/206 CH62/6/2008-152). The study has been registered on the Australia New Zealand Clinical Trials Registry (ACTRN: 12608000334303).

### Subjects

Hospitalised, adult patients initiated on warfarin during admission or continuing pre-admission therapy are eligible for inclusion in the study. The inclusion and exclusion criteria are detailed in Table 2.

**Table 2 T2:** Inclusion and exclusion criteria

Inclusion Criteria	Exclusion Criteria
• hospital inpatients who were to be discharged on warfarin (newly commenced or taking it upon hospital admission)	• patients suffering from lupus anticoagulant or antiphospholipid syndrome
• indications for anticoagulation, including atrial fibrillation, venous thromboembolism (deep vein thrombosis and/or pulmonary embolism) and prosthetic valve replacement	• residents of aged care facilities and others not eligible for a HMR
• intended duration of anticoagulation of a minimum of 3 months	• patients with dementia, or otherwise unable to answer basic questions about their therapy
	• patients without a regular general practitioner and community pharmacist through which an HMR could be arranged
	• patients entering Hospital in the Home, Patients Acute Treatment and Care in the Home, Acute/Post-Acute Care or similar outreach programs

### Sample size

Based on sample size calculations, groups comprising approximately 120 patients in each (control, 2-visit model, and 3-visit model) are estimated as being statistically adequate. This is based on the previous RCT of this model of care where 10% of the usual care group experienced a major bleeding event within 90 days post-discharge, which was reduced to 2% in the intervention group [36]. Using these figures, approximately 108 patients are needed per group at a power of 80% and p = 0.05. Published data are also available indicating that approximately 30-40% of patients commenced on warfarin experience a bleeding complication within 3 months [16,18,36,45]. The aim of the intervention program is to reduce this figure to below 10%, in which case approximately 72 patients are needed per group at a power of 80% and p = 0.05. The proposed recruitment targets are thus 160 in the control group and 240 in the intervention group (120 receiving the 2-visit model and 120 the 3-visit model).

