### Statistical analysis

Demographic data will be utilised to compare the control and intervention groups for a range of parameters (e.g. age, gender, PhARIA class, living and medication management arrangements, co-morbidities, warfarin drug interactions) using independent samples t-testing for continuous data and chi-squared analysis for categorical data. Outcome data will be reported using parametric statistics, with independent samples t-testing utilised for the majority of continuous variables and chi-squared analysis for the majority of discrete variables. Data will be statistically analysed across the 3 groups (control, Level 1 Service, and Level 2 Service). For the evaluation questionnaires, responses will be recorded on modified Likert scales, with 0 representing "Strongly agree" and 10 "Strongly disagree". Qualitative feedback will obtained via open-ended questions. Data analysis will involve descriptive statistics and thematic analysis of the qualitative responses.

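### The 108 per group for 10% vs 2% does not reproduce for a two-sided two-group comparison (138, or 162 continuity-corrected) and rests on a different convention from the 72 beside it

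*Protocol article*

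**What the plan says.** All of the sizing is in one paragraph of the protocol article, under Sample size.

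- It opens with the statement that "groups comprising approximately 120 patients in each (control, 2-visit model, and 3-visit model) are estimated as being statistically adequate".
- The primary-outcome calculation takes its rates from the previous randomised trial, in which "10% of the usual care group experienced a major bleeding event within 90 days post-discharge", "which was reduced to 2% in the intervention group". It then concludes: "Using these figures, approximately 108 patients are needed per group at a power of 80% and p = 0.05".
- A second calculation concerns bleeding complications of any kind, put at roughly 30-40% within three months, with the aim of bringing this below 10%, "in which case approximately 72 patients are needed per group at a power of 80% and p = 0.05".
- It closes: "The proposed recruitment targets are thus 160 in the control group and 240 in the intervention group", the latter split into 120 per service level.

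The paragraph does not state the number of sides, the formula or any continuity correction. Under Statistical analysis, the article plans "chi-squared analysis for the majority of discrete variables" and says that data will be analysed across the three groups (control, Level 1, Level 2). No one-sided hypothesis is declared anywhere.

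**The concern.** Both per-group figures carry the same label, 80% power at p = 0.05, so a reader will assume one method. With no direction declared and a chi-squared analysis planned, that reader will also assume a two-sided comparison. On that basis 108 is too small for 10% vs 2%, and the 80% attached to it is not what 108 patients per group deliver when one group is compared with another.

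What is at stake is the stated justification for the primary outcome. Someone who later reads a non-significant result for one service level against control would take the chance of detecting the assumed effect at the quoted size to be 80%, when it is nearer 70%. The step from these requirements to 160 controls is not explained either.

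**Working it through.** **Inputs.** p1 = 0.10, p2 = 0.02, alpha = 0.05, power = 0.80, equal groups (all from Sample size). Difference d = 0.08; mean p̄ = 0.06. z for power = 0.8416; z for alpha = 1.6449 one-sided, 1.9600 two-sided.

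**Formula (pooled variance under the null).** n = [zα√(2p̄(1−p̄)) + zβ√(p1(1−p1) + p2(1−p2))]² / d²

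√(2 × 0.06 × 0.94) = 0.3359; √(0.09 + 0.0196) = 0.3311; second term 0.8416 × 0.3311 = 0.2786.

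*Step 1: reproduce 108.* One-sided: (0.5524 + 0.2786)² / 0.0064 = 107.9, so 108.

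*Step 2: two-sided.* (0.6583 + 0.2786)² / 0.0064 = 137.2, so 138.

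*Step 3: two-sided with continuity correction.* n′ = (n/4)[1 + √(1 + 4/(nd))]². With n = 137.15: 4/(137.15 × 0.08) = 0.3646 and n′ = 34.29 × (2.168)² = 161.2, so 162.

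*Step 4: other equal-group formulas.* Two-sided unpooled 135, two-sided arcsine 122. By exact binomial enumeration, the uncorrected chi-squared test reaches 80% at about 126. All exceed 108. One-sided unpooled gives 106, one-sided arcsine 96 and one-sided corrected 132.

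*Step 5: the companion figure, 30% vs 10%.* p̄ = 0.20, d = 0.20. Two-sided: (1.1087 + 0.4610)² / 0.04 = 61.6, so 62. With correction: 4/(61.6 × 0.2) = 0.325 and 15.4 × (2.151)² = 71.2, so 72. One-sided gives 49, or 58 corrected. The upper end of the range, 40% vs 10%, gives 32 two-sided and 38 corrected. So 72 matches two-sided with correction at the 30% end.

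**Two-sided pairwise power, 10% vs 2%.** Normal approximation: Φ[(d − 1.96·s0)/s1], where s0 = √(p̄(1−p̄)(1/n1 + 1/n2)) with p̄ weighted by group size, and s1 = √(p1(1−p1)/n1 + p2(1−p2)/n2).

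| Groups | s0 | s1 | Normal approx. | Exact, uncorrected | Exact, Yates |
|---|---|---|---|---|---|
| 108 vs 108 | 0.0323 | 0.0319 | 70% | 73% | 61% |
| 120 vs 120 | 0.0307 | 0.0302 | 75% | 79% | 67-68% |
| 160 vs 120 | 0.0299 | 0.0269 | 79% | 83% | 72% |
| 160 vs 240 | 0.0227 | 0.0254 | 92% | 94% | 91% |

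**Three-group chi-squared test (2 degrees of freedom), 10%/2%/2%.** Noncentrality λ = Σ nᵢ(pᵢ − p̄)² / [p̄(1−p̄)].

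- 108 each: λ = 0.4608/0.0445 = 10.4, power about 83% (81% when the approximation is checked directly).
- 120 each: λ = 10.36 × 120/108 = 11.5, about 87% (85% checked directly).
- 160/120/120: λ = 0.6144/0.0493 = 12.5, about 90%.

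None of these powers allows for loss to follow-up or multiple comparisons.

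**The case against.** The strongest reply is that the trial as targeted does not suffer. The size of 108 is a computed minimum and 120 a size judged adequate; recruitment is aimed at 160, 120 and 120. At those sizes the uncorrected chi-squared test exceeds 80% by exact enumeration for each level against control and for the pooled comparison. The analysis literally described, across three groups, exceeds 80% even at 108 per group if both levels achieve 2%. All of this stands. A reader might infer from the 70% and 75% that the study is underpowered for its planned test. The article does not support that: it does not name a pairwise test as primary, and those percentages belong to sizes below the control target.

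Second, neither sidedness nor formula is stated, so calling 108 one-sided is an inference from the match. The quoted rates may also be rounded: a two-sided pooled calculation gives about 108 at 10.5% vs 1.5%. That is the very edge of rounding and an unlikely explanation, but the cause cannot be settled from the article. The match for 72 likewise depends on taking 30% from a range and exactly 10% for a target below 10%. These points limit what can be said about how the figures arose. They do not make 108 correct for the rates as printed.

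Third, a reader might see 120 and 160 controls as a contradiction. They are an adequate size and a recruitment target, and a target may exceed a minimum. What is left is a *thus* with no reasoning behind it.

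Finally, an article may leave method details to a fuller document. But 108 is a printed number that can be checked against its own printed inputs.

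**Conclusion.** The figure of 108 is wrong as written for a two-sided two-group comparison of 10% vs 2%. The pooled formula gives 138, which is 30 more per group (30/108 = 28%); the continuity-corrected formula gives 162; the most lenient two-sided calculation tried gives 122. The 108 and the 72 do not share a convention on the stated inputs: the method that yields 72 would require 162 for the primary outcome.

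The consequence is modest. Pairwise power is about 70% (exact 73%) at 108 and 75% (exact 79%) at 120 per group. At the targets it is about 79% (exact 83%) for each level against control and 92% (exact 94%) for the pooled intervention. This is a correction to the stated basis of the sample size and does not show that the recruitment targets are inadequate. It rests on the article's rates, complete follow-up, no multiplicity adjustment and, for the three-group and pooled figures, 2% in both service levels.

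**What to change.** Rewrite the Sample size paragraph:

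1. State that the calculation is two-sided, and name one formula for both figures.
2. Replace 108 with 138 and 72 with 62 (uncorrected), or with 162 and 72 if continuity correction is intended. Give the rates used for the second figure (30% vs 10%).
3. State power at 160/120/120: about 79% for each level against control and 92% for the pooled intervention, uncorrected. If continuity correction is adopted, the exact Yates figures are 72% and 91%. If the three-group test is the intended analysis, quote its power of about 90% and the assumption of 2% in both levels.
4. Say why the control target is 160 when about 120 per group is called adequate.

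The cost is one rewritten paragraph and a slightly less favourable power for each level. The correction needs no extra patients and leaves the endpoint and the planned analysis unchanged.
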